### Study end points

The primary outcome is the incidence of clinically significant DB, defined as anal blood loss occurring after the completion of the procedure necessitating emergency department consultation, blood transfusion, prolongation of hospital stay, re-hospitalization, or re-intervention (either repeat endoscopy, angiography or surgery) [5, 10, 20–23]. Self-limiting bleeding managed on an outpatient basis is not considered to be DB.

PC may improve patients’ health status, prevent serious complications of DB, reduce the demand for healthcare, and lower costs. The secondary outcomes therefore are (1) severity of DB (see Supplementary File 1 for definition of DB severity), (2) procedure time, (3) perforation rate, (4) EMR scar evaluation at the first surveillance colonoscopy after 6 months, (5) adenoma recurrence rate at 6 months, (6) health-related quality of life, and (7) direct and indirect costs related to PC.

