**Interventions:**							
***PC post EMR***			X				
***Questionnaires (EQ-5D*****,** ***iMCQ*****,** ***iPCQ)***			X	X	X	X	
***Control group without PC***			X				

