### Data collection and management

Coded study data will be collected in a web-based case record form (CRF) in Castor EDC. Patients will have the option to fill out the questionnaires with the end-to-end encrypted mobile “Improve” app (Open HealthHub, Utrecht, The Netherlands). After the data collection is complete, data are locked and saved for 15 years according to national law and regulations.

Missing data within a complete follow-up term will be prevented as much as possible. The reason for missing data will be reported. In case of > 5% non-selective missing data, multiple imputation may be performed. Sensitivity analyses will be performed with a different assumption for the distribution of the missing data than that was used in the primary analysis [24, 25].

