### Statistical analysis methods

#### Primary analysis

Comparison of the primary endpoint DB will be performed according to intention-to-treat, using a mixed model regression analysis to correct for clustering of data, resulting in an estimated relative risk and 95% confidence intervals. Scale variables will be presented as mean ± standard deviation and in case of skewed distributions as median and range. Values will be compared by Student’s *T* test, Wilcoxon rank sum test, *χ*^2^ test, or Fisher exact test as appropriate. A two-tailed *p* value < 0.05 is considered statistically significant. A type 1 error will be controlled for by only taking one presentation of the primary endpoint (DB) per patient in the statistical analysis. In case of multiple presentations for bleeding, the highest gradation for severity will be included in the analysis. The outcomes of the intention-to-treat analysis will be compared to an exploratory per-protocol analysis.

In case of disbalances in baseline characteristics, potential confounders for DB will be determined with a *χ*^2^ test or unpaired *t* test where appropriate. Correction for potential confounders with a *p* ≤ 0.15 will be performed using multiple regression analysis. Considering the expected incidence of DB, the statistical power will allow to correct for two confounding factors. We expect at least anticoagulant medication to be a potential confounder for DB.

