#### Analyses of secondary outcomes

The secondary endpoints will be compared between study groups using Student’ *T* test or *χ*^2^ test whenever appropriate. Lastly, a cost-effectiveness analysis will be performed. As a societal perspective allows for a more complete economic evaluation as compared to a health care perspective alone, three cost categories will be analyzed: direct medical costs, direct non-medical costs, and indirect costs (see Supplementary File 1 for a definition of these secondary endpoints).

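### Quality of life is measured four times but assigned a t-test, which uses neither the first score nor the correlation between visits: valid with complete data, but less precise than it need be

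*Protocol article*

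**What the plan says.** Study end points lists "6) health-related quality of life" among the secondary outcomes. In Table 1 the row beginning "Questionnaires (EQ-5D" is marked at four times: EMR+0, 1, 3 and 6 months. The first mark stands in the post-allocation EMR+0 column. None stands under week −1 or under allocation.

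Analyses of secondary outcomes states that "The secondary endpoints will be compared between study groups using" a Student's t-test or a chi-square test, as appropriate. No other method is named for quality of life.

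Three other places bear on the point:

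- Primary analysis names a mixed model, but for delayed bleeding only: "Comparison of the primary endpoint DB will be performed according to intention-to-treat, using a mixed model regression analysis to correct for clustering of data".
- Data collection and management says "In case of > 5% non-selective missing data, multiple imputation may be performed", and adds "Sensitivity analyses will be performed with a different assumption for the distribution of the missing data than that was used in the primary analysis".
- Economic evaluation turns the EQ-5D scores into one QALY per patient for the cost-utility ratio. It foresees regression on net monetary benefit if baseline imbalance calls for it. Neither is said to be the quality-of-life comparison.

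**The concern.** A t-test takes one value per patient. Applied to an outcome with a first score and three follow-ups, it leaves the patient's own starting level in the error term and does not let an answered visit inform a missed one.

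Precision matters more than usual here. If clipping affects quality of life mainly by preventing bleeds (an assumption), the effect is spread over an arm in which few patients bleed: the planned difference is 9.8% − 2% = 7.8 percentage points. The mean difference in EQ-5D will then be small, and the width of the confidence interval decides how much the result says.

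Missing questionnaires are the second issue. The imputation provision is optional and confined to non-selective missingness, the situation in which an analysis of responders is least biased anyway. What happens under selective non-response is left to sensitivity analyses.

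**Working it through.** **Inputs from the article.** 178 patients per arm and 15% drop-out (Sample size considerations); EQ-5D at four times (Table 1). The only sample-size figure concerns delayed bleeding. It reproduces: 155 per arm gives 80.2% power with Fisher's exact test at 4.9%, and 310 × 1.15 = 356.5 against the stated 356. There is no planned figure for quality of life to reproduce.

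**Assumptions.** The same correlation r between any two visits, shown over a range because the article gives none. The 15% trial drop-out stands in for questionnaire non-response, so 178 × 0.85 ≈ 151 per arm answer a visit.

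**Step 1: t-test at one visit.** Detectable difference at 80% power, two-sided 5%: (1.960 + 0.842) × √(2/151) = 0.322 SD.

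**Step 2: adjust for the first score.** The variance is multiplied by 1 − r², and the standard error and detectable difference by √(1 − r²).

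| r | 1 − r² | Fall in standard error | t-test patients per arm for equal precision, 151/(1 − r²) | Detectable difference (SD) |
|---|---|---|---|---|
| 0.3 | 0.91 | 4.6% | 166 | 0.308 |
| 0.5 | 0.75 | 13.4% | 201 | 0.279 |
| 0.6 | 0.64 | 20.0% | 236 | 0.258 |
| 0.7 | 0.51 | 28.6% | 296 | 0.230 |

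A simulation of 4,000 trials (SD 0.2, 15% missing at random at 6 months) agrees: standard errors of 0.0229 against 0.0198 (r = 0.5), 0.0231 against 0.0185 (0.6) and 0.0230 against 0.0165 (0.7), which are falls of 13.5%, 19.9% and 28.3%.

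**Step 3: average of the three follow-ups.** Relative to one visit, the variance of the unadjusted average is (1 + 2r)/3, and with the first score (1 + 2r)/3 − r². For r = 0.5, 0.6 and 0.7 these are 0.667, 0.733, 0.800 and 0.417, 0.373, 0.310. The average answers a different question from a single visit. If the effect were confined to month 1, averaging would divide it by three, and the signal-to-noise ratio relative to a plain 1-month t-test would be (1/3)/√0.417 = 0.52 at r = 0.5 and (1/3)/√0.310 = 0.60 at r = 0.7. To break even, the averaged effect must be at least √0.310 = 0.56 (r = 0.7) to √0.417 = 0.65 (r = 0.5) of the 1-month effect.

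**Step 4: missing questionnaires.** Simulation with 178 per arm, no true difference, 3,000 trials per scenario, about 13 to 15% missing at the last visit. Bias of the responder-only difference:

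- missing completely at random: 0;
- missingness depending on the previous score equally in both arms: 0;
- missingness depending on the previous score in one arm only: −0.053 SD (r = 0.5) and −0.072 SD (r = 0.7).

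An estimator using the first and earlier scores had bias of at most 0.002 SD in every scenario.

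**The case against.** The strongest reply is that this is a condensed article, and that a t-test between randomised groups is valid. The wording lets the test be chosen as appropriate, and a t-test on a per-patient summary such as the QALY would comply with it and would combine the visits. This stands in part. With complete data the issue is efficiency, not validity. But the stated choice lies between two tests, neither of which uses a first score or repeated visits, and the QALY is assigned to the cost-utility analysis. The article fixes a method here; it does not merely leave one open.

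Four stronger readings are tempting, and the documents do not support them:

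- *That only responders will be analysed.* Data collection and management allows multiple imputation above 5% non-selective missingness and commits to sensitivity analyses.
- *That non-response related to health must bias the t-test.* In Step 4 bias arose only when the dependence differed between arms. Nothing in the article shows that it will, although patients under conscious sedation cannot be blinded, so it is conceivable.
- *That separate tests at each visit are planned, with the best one to be picked.* The article does not say this. Choice of visit is a detail that an analysis plan commonly settles.
- *That the variance falls to 42%, 37% or 31%.* Those figures compare a three-visit average with one visit. Part of the gain comes from averaging alone, which a t-test on the patient's mean would share.

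**Conclusion.** The point holds as one of efficiency, with a limited and conditional risk of bias. The stated test gives up about 5% of the standard error at r = 0.3 and up to 28 to 29% at r = 0.7, for a single-visit difference. These figures rest on an assumed, equal correlation between visits and on a first score that can be used as a baseline.

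The possible attrition bias, about 0.05 to 0.07 SD in the scenarios tried, needs non-response that depends on earlier scores differently by arm. It is a risk that the optional imputation rule does not remove, not a demonstrated bias.

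The gain should not be oversold. Acting only through the planned 7.8-point difference in bleeding, a bleed would have to lower the score by 0.322/0.078 = 4.1 SD to reach the t-test's detectable difference, and still by 0.230/0.078 = 2.9 SD at the best adjusted value in Step 2. The benefit is a narrower interval for a secondary outcome. The trial's conclusion on delayed bleeding is untouched.

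**What to change.** For quality of life, replace the t-test by one linear mixed model of the EQ-5D index at 1, 3 and 6 months, with arm, visit, arm-by-visit and the first EQ-5D score as covariate, and correlated errors within patient.

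- **First score.** Confirm that it is completed before randomisation, which takes place after the resection. Table 1 puts it in the post-allocation column. If this cannot be confirmed, fit the repeated-measures model without it. The gain of Step 2 is then not available; what remains is the use of partly answered follow-up.
- **Main contrast.** Name one in advance: the 1-month difference or the follow-up average, chosen by when a bleeding-related effect is expected, given that the primary outcome covers 30 days. Report its 95% confidence interval and give the other visits as supportive.
- **Missing data.** State how the imputation and sensitivity provisions apply to this outcome, including selective non-response.

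The cost is analysis-plan wording and slightly more modelling, with no new patients, visits or questionnaires. The model relies on a missing-at-random assumption, which the planned sensitivity analyses can test.

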#### Economic evaluation

All costs will be estimated in accordance with Dutch guidelines concerning cost-effectiveness studies [26, 27]. The price of clipping will be calculated based on the price of the Quick Clip Pro - Single Use Repositionable Clip (Olympus, Japan) in the Netherlands. Health care cost utilization and productivity losses will be estimated based on customized versions of the standardized questionnaires iMTA MCQ (Medical Cost Questionnaire) and iMTA PCQ (Productivity Cost Questionnaire). Loss of paid and unpaid work will be valued by means of the friction cost approach. Complete costs will be calculated for individual patients by multiplying actual health care resource use and unit prices [28, 29] and will be compared directly between study groups.

The impact of morbidity on the quality of life of patients will be assessed by the EQ-5D questionnaire. The individual scored items will be valued by the Dutch tariff. Health Utility Index scores will be used to derive a quality-adjusted life year (QALY) estimate for each patient [30, 31]. Incremental cost-effectiveness and cost-utility ratios will be calculated to reflect the extra costs per patient with poor outcome prevented and the extra costs per additional QALY respectively. Uncertainty in the cost-effectiveness ratio will be presented non-parametrically using bootstrap techniques. If correction for baseline disbalances is needed, regression techniques including bootstrapping will be used with the Net Monetary Benefit as outcome parameter. Results will be shown graphically by means of a cost-utility plane and cost-effectiveness acceptability curves with varying values of willingness-to-pay up to €80.000.

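### The cost-utility analysis adjusts for baseline only if correction is judged to be needed; adjusting for baseline EQ-5D utility in every case would be more precise and would remove a data-dependent choice of model

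*Protocol article*

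**What the plan says.** The Economic evaluation section of the protocol article values EQ-5D responses by the Dutch tariff and then derives one QALY figure per patient: "Health Utility Index scores will be used to derive a quality-adjusted life year (QALY) estimate for each patient". Of total costs it says that they "will be compared directly between study groups". Uncertainty in the ratio is bootstrapped, and acceptability curves are drawn for "varying values of willingness-to-pay up to €80.000". Baseline enters in one place only: "If correction for baseline disbalances is needed, regression techniques including bootstrapping will be used with the Net Monetary Benefit as outcome parameter".

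Two neighbouring sections take a similar line. Analyses of secondary outcomes, which covers quality of life, gives unadjusted tests: "The secondary endpoints will be compared between study groups using Student’ *T* test or *χ*^2^ test whenever appropriate". Primary analysis uses look-then-adjust for bleeding, there with a threshold: "Correction for potential confounders with a *p* ≤ 0.15 will be performed using multiple regression analysis".

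Table 1 places the questionnaires at the time of EMR and at 1, 3 and 6 months. The first of these stands in the post-allocation block. None is listed at enrolment or in the allocation column.

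**The concern.** In a randomised trial, any baseline difference is due to chance. The reason to adjust for a covariate is that it predicts the outcome, not that it happens to look unbalanced. Baseline utility does so twice here: it is the first point of the area that makes up the QALY, and it is likely to correlate with the later utilities. An unadjusted QALY difference therefore carries part of whatever baseline difference occurred, including differences too small to prompt correction.

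A rule that adjusts only when someone judges it necessary leaves the smaller differences in place, gives up precision in most trials, and lets the observed data choose the model. The QALY gain to be expected from preventing a few bleeds is small, so precision matters. Cost-effectiveness is a stated aim of the trial, but the sample size is derived for bleeding alone.

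**Working it through.** **Figures from the plan.** The article gives no figure for the cost-utility analysis; its sample size supplies only the number per arm. Exact power of Fisher's test at 155 per arm (9.8% against 2%, two-sided 4.9%) is 80.2%, which agrees with the stated 310. Then 310 × 1.15 = 356.5, the stated 356 or 178 per arm. The plan also gives the bleeding reduction of 7.8 points and the ceiling of EUR 80,000 per QALY.

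**Assumptions, not in the article.** Utility SD 0.20 (range 0.15 to 0.25), between-visit correlation 0.3 to 0.7, baseline-QALY correlation ρ of 0.4 to 0.7, QALY SD 0.10, and a utility loss of 0.1 to 0.5 for one month per bleed.

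**1. How much chance imbalance reaches the QALY difference.** The trapezoid over 0, 1, 3 and 6 months gives weights of 0.042, 0.125, 0.208 and 0.125 years. The slope of QALY on baseline utility is 0.042 + r × 0.458, which is 0.179, 0.271 and 0.363 for r = 0.3, 0.5 and 0.7. At 155 per arm, the SE of the baseline difference is 0.20 × √(2/155) = 0.0227.
- One SE carries 0.0227 × 0.179 to 0.0227 × 0.363, or 0.004 to 0.008 QALY.
- A difference just short of p = 0.05 (1.96 × 0.0227 = 0.0445) carries 0.008 to 0.016 QALY, about EUR 640 to 1,290 at EUR 80,000.
- For scale, the gain from fewer bleeds is 0.078 × 0.1 × 1/12 = 0.0007 to 0.078 × 0.5 × 1/12 = 0.003 QALY. It would be larger if the loss lasted longer.

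**2. Always against never adjusting.** The interval narrows by 1 − √(1 − ρ²). For ρ = 0.4 this is 1 − √0.84 = 8%; for ρ = 0.7 it is 1 − √0.51 = 29%.

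**3. Always against conditional adjusting.** Take ρ = 0.6, QALY SD 0.10 and 178 per arm. With trigger value c for the standardised baseline difference Z, the variance relative to never adjusting is (1 − ρ²) + ρ² × E[Z²; |Z| ≤ c].

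| Rule | E[Z²; \|Z\| ≤ c] | Relative variance | SD of QALY difference |
|---|---|---|---|
| Never | 1 | 1 | 0.10 × √(2/178) = 0.0106 |
| Trigger p < 0.05 (c = 1.96) | 0.721 | 0.64 + 0.36 × 0.721 = 0.900 | 0.0100 |
| Trigger p ≤ 0.15 (c = 1.44) | 0.443 | 0.64 + 0.36 × 0.443 = 0.799 | 0.0095 |
| Always | 0 | 0.64 | 0.0085 |

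At 155 per arm every SD is larger by √(178/155) = 1.07, and the comparison between rules is unchanged.

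A separate simulation (8,000 trials, 155 per arm, no treatment effect) gave variance under the conditional rule of 1.25, 1.56 and 2.44 times that of always adjusting for between-visit correlation 0.3, 0.5 and 0.7 with trigger p ≤ 0.05, and 1.16, 1.35 and 1.90 times with p ≤ 0.15. About 95% and 85% of trials stayed unadjusted, as the triggers imply. The nominal 5% test rejected in 1.9% to 4.6% of trials.

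**4. Net monetary benefit.** Assume in addition that costs are independent of utility, with SD EUR 2,000 to 8,000. The interval ratio is √[(λ² × 0.01 × 0.64 + SD²) / (λ² × 0.01 + SD²)].
- λ = EUR 80,000: √(44.96/68) = 0.81 to √(104.96/128) = 0.91, so 19% to 9% narrower than with no adjustment.
- λ = EUR 20,000: √(6.56/8) = 0.91 to √(66.56/68) = 0.99, so 9% to 1% narrower.

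**5. Sign of the QALY difference.** At a true gain of 0.003, the chance of a wrong sign is Φ(−0.003/0.0100) = 38% under the conditional rule (p < 0.05) and Φ(−0.003/0.0085) = 36% with adjustment always.

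**The case against.** The strongest defence is that nothing invalid is shown. The unadjusted difference is unbiased over randomisation, a bootstrap interval already contains chance baseline variation, and the conditional rule makes the test conservative. The primary endpoint and sample size are untouched. All of this stands, and it limits the point to precision, to error conditional on the imbalance observed, and to a model chosen by the data.

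A second defence is that the article is condensed, so the criterion for correction and the list of covariates may sit in the full protocol or analysis plan. This also stands, and the absence of a threshold is not held against it. But the conditional rule itself is stated, and an analysis plan that follows it keeps the fault. Because no trigger is given here, both p < 0.05 and p ≤ 0.15 are shown; the latter is borrowed from the primary analysis and is the more favourable to the plan.

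Third, the article speaks of direct comparison for costs only. That the QALY comparison is unadjusted by default is a reading of the conditional sentence together with the unadjusted tests for secondary outcomes. It is a reasonable reading, not an explicit statement.

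Fourth, a true baseline EQ-5D may not exist. Table 1 shows the first questionnaire after allocation, and the Blinding section accepts that patients under conscious sedation cannot be blinded. At publication 217 patients had been randomised. This stands as a condition on the fix. It applies equally to the plan's own conditional correction if that uses utility.

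**Conclusion.** The point holds as one of efficiency and pre-specification in a secondary evaluation. Adjusting for baseline utility in every case is the better rule, and it uses a method and a questionnaire that are already planned. Under the stated assumptions, the QALY interval is about 8% to 29% narrower than with no adjustment. Against a conditional rule at correlation 0.6, the SD falls from 0.0100 or 0.0095 to 0.0085, a reduction of about 15% or 11%. For net monetary benefit the gain over no adjustment runs from about 1% to 19%, depending on cost variance and willingness to pay. The sizes rest on assumed SDs and correlations; the direction needs only that baseline and later utility are correlated.

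Two stronger readings are not supported. A reader might infer that the conditional rule biases the result or produces false positives: randomisation and the simulated rejection rates say otherwise. A reader might also infer, because a chance imbalance can carry more QALYs than the expected gain, that adjustment would secure the sign of the result. It would not: a wrong sign goes only from about 38% to 36%, because noise in the later utilities remains.

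**What to change.** State that the bootstrapped regression on net monetary benefit is the main cost-utility analysis whatever imbalance is observed, with arm and baseline EQ-5D utility as terms, and centre, the stratification factor, if it can be estimated across the 19 hospitals. Use the same baseline-utility adjustment for the QALY difference. Report the unadjusted comparison as supplementary.

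First establish when the EQ-5D at the time of EMR was completed, and record this per patient if possible. Where it was completed before allocation, or could not have been affected by it, use it as the baseline covariate. Where that cannot be shown, do not treat it as one without a sensitivity analysis.

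The cost is a short change of wording and slightly more analysis work. The real dependency is the timing of that questionnaire, which may not be recoverable for patients already randomised.

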### Monitoring

#### Data monitoring

According to the Dutch Federation of Universities (NFU) standard for risk assessment and monitoring, the trial was graded as having a negligible risk for participants. Therefore, no Data Safety Monitoring Board or Data Monitoring Committee was indicated. Nonetheless, a blinded OAC comprising 3–4 independent gastroenterologists will assess and weigh all severe adverse events after completion of the trial and decide whether these concord with definitions of the study endpoints. Using primary source data and blinded for treatment allocation (if possible), each member of the committee will individually evaluate the disease course of each patient. Disagreements will be resolved at a plenary consensus meeting. Only after consensus has been reached on each individual endpoint, a final analysis will be performed.

